## Abstract

**Background:**

In the UK, type 2 diabetes mellitus (T2D) is largely managed in primary care. Delay in the intensification to injectable therapy, a form of clinical inertia, is associated with worse glycaemic control. UK general practice is highly computerised, with care being recorded on computerised medical record systems; this allows for quantitative analysis of clinical care but not of the underpinning decision-making process. The aim of this study is to investigate perceptions of patients and clinicians in primary care on the initiation of injectable therapies in T2D, and the context within which those decisions are made.

**Methods:**

This is a mixed methods study, taking a “realist evaluation” approach. The qualitative components comprise focus groups, interviews, and video recordings of simulated surgeries; the quantitative analysis: an overview of participating practices, elements of the video recording, and an online survey. We will recruit primary care clinicians (general practitioners and nurses) and patients from a representative sample of practices within the Royal College of General Practitioners (RCGP) Research and Surveillance Centre (RSC) network. Participants will be patients with T2D, and primary care clinicians. Focus groups and semi-structured interviews will be recorded, transcribed *verbatim* and analysed using Framework Analysis. The simulated surgeries will include cases that might be escalated to injectable therapy. The consultation will be reviewed using the Calgary-Cambridge model to assess communication and determination of adherence to national prescribing guidelines. We will conduct multi-channel video recording including screen capture, clinician and patient facial expressions, wide angle view of the consultation, and the computerised medical record screen. This allows annotation and qualitative analysis of the video recordings, and statistical analyses for the quantitative data. We will also conduct an online survey of primary care clinicians’ attitudes to, and perceptions of, initiation of injectable therapies, which will be analysed using summary statistics.

**Discussion:**

Results aim to provide a detailed insight into the dynamic two-way decision-making process underpinning use of injectable therapy for T2D. The study will provide insights into clinical practice and enable the development of training, interventions and guidelines that may facilitate, where appropriate, the intensification to injectable therapy.

**Electronic supplementary material:**

The online version of this article (10.1186/s12913-019-4112-3) contains supplementary material, which is available to authorized users.

## Background

Type 2 diabetes (T2D) is a major problem for many health care systems [1–8]. The World Health Organisation (WHO) has estimated that there are approximately 422 million people in the world with T2D [1]. Following analyses of the Framingham study in the 1970s it became clear that T2D is a major risk factor for macrovascular disease (including myocardial infarction and stroke), and studies since have demonstrated that macrovascular risk increases with worsening glycaemic control [9, 10]. Diabetes is also associated with an increased risk of microvascular complications which includes diabetic retinopathy, neuropathy, and renal disease [11]. Several landmark trials have demonstrated that risk for both microvascular and macrovascular complications of diabetes can be reduced by improving blood glucose control [12–15].

National and international guidelines have provided targets for optimum glycaemic control, which have been established through observational evidence and clinical trials [16–22]. However, adequate glycaemic control is difficult to achieve for a significant proportion of people with T2D. In a large-scale European study, real-world diabetes care was compared against the glycaemic targets produced by the American Diabetes Association (ADA) and European Association for the Study of Diabetes (EASD), and found that only 53.6% of people with T2D achieved adequate glycaemic control, with considerable variation between countries [23].

In the UK, T2D is largely managed in primary care, reinforced by pay-for-performance (P4P) in general practitioners’ contracts [2, 3, 24] - a scheme called the Quality and Outcomes Framework (QOF). UK general practice consultations are recorded into computerised medical record (CMR) systems which actively flag whether a patient with T2D is at target. Rewards paid through the P4P system, QOF, are solely based on information recorded in CMR systems. These computerised systems record the diagnosis of T2D and link to pathology services allowing transfer of glycated haemoglobin (HbA1c) data to the individual’s medical records. CMR systems also record all the prescriptions issued in primary care. Additionally, most brands of CMR systems prompt the primary care clinician at every consultation if a person with T2D is not at their glycaemic target. Therefore, every time a person with T2D presents to their general practitioner (GP) or other primary care clinician, the clinician can readily tell if they are at target, and generally with one mouse click, whether they are receiving maximal oral therapy [25].

QOF remuneration targets for T2D include optimising the number of people below set glycaemic thresholds. CMR based interventions are known to generally improve care [25] and the introduction of these P4P targets appear to have improved glycaemic control and reduced inequalities in T2D management [26, 27]. However, it is difficult to disentangle these effects from other quality improvement initiatives.

One component of suboptimal management is delay in intensification of therapy. Delays in intensification occur at each stage of treatment: from diagnosis to first oral medication, to second and third oral medications, to the initiation of injectable therapies and escalation of injectable therapies once initiated [28]. These delays termed “therapeutic inertia” or, more commonly “clinical inertia” [29], are associated with impaired glycaemic control and concomitant complications including microvascular (e.g. retinopathy, chronic kidney disease) and macrovascular diseases (e.g. heart failure, stroke) [30]. Despite improved glycaemic control following the use of injectable therapy, drawbacks of insulin include weight gain, and severe hypoglycaemia and increased risk of death [31, 32], whilst glucagon-like peptide 1 receptor agonists (GLP-1 RAs) have been linked to gastrointestinal symptoms such as nausea, vomiting, and diarrhoea [33], which may deter people from using them. Other barriers to starting injectable therapy include the individual struggling to acknowledge that their diabetes has progressed, anxiety and fear of pain from injecting, the need to regularly test blood glucose levels, and the difficulty incorporating injecting during working hours [34–36].

Clinician, patient, and health service factors have been identified as contributing to clinical inertia [37–44]. However, an improved understanding of the specific patient, clinician, and health service factors that influence clinical inertia is urgently needed to facilitate improved glycaemic control and health outcomes in people with T2D.

## Aims and objectives

The aim of this study is to explore the perceptions of patients and clinicians regarding the initiation of injectable therapies: insulin and GLP-1 RAs, and to describe the context within which these decisions are made.

The primary objectives of this study are:To explore the attitudes and experiences of patients with T2D and primary care clinicians (GPs and nurses) of barriers and facilitators to initiating injectable therapies.To describe the context and processes in which injectable therapy initiation would take place; in particular how computerised prompts are managed.To describe any consensus or discrepancies within and between clinicians and patients about attitudes to intensification to injectable therapies.

## Methods

### Study design and setting

This study combines qualitative and quantitative methods, and should be regarded as a mixed methods study [45–47]. It will be run within the Royal College of General Practitioners (RCGP) Research and Surveillance Centre (RSC) sentinel network of general practices (35, 36). The qualitative methods comprise focus groups that will be carried out with a sample of practices. Interviews will be used if patients or clinicians are unable or uncomfortable with participating in focus groups. The subsequent quantitative component will include a comparison of initial themes on injectable therapy drawn from an earlier phase of the study, with other practices in the network via a survey to explore consensus. We will also carry out a video study to provide quantitative data on key prompts/triggers for the initiation of injectable therapy raised during a consultation with a simulated T2D patient.

We will recruit participants from volunteer practices within the RCGP RSC network, [48, 49]; our aim is to recruit practices that are representative of the network. The RCGP RSC data have been used extensively for diabetes research, and although there are limitations in case finding, recording of pathology results, and in recording of therapies, the network has good data quality and is largely nationally representative [48].

The research project will be run in three phases: Phase 1: Focus groups and interviews; Phase 2: Video recording of simulated surgeries with follow-up focus groups; and Phase 3: Survey, consensus exercise (Fig. 1). The qualitative processes will follow the Consolidated Criteria for Reporting Qualitative Research (COREQ) checklist [50].

**Fig. 1 Fig1:**
[figure not shown]
Overview of the study phases

### Philosophical approach

We have defined, a priori, critical realism as an overall philosophical approach. This approach is appropriate because the decisions to intensify therapy in the clinical consultation are complex [51]. The Medical Research Council framework for Complex Intervention includes key elements of critical realism, in particular the need to define the context and mechanism [52].

#### Realist evaluation

We will use Pawson and Tilley’s “realist evaluation” to provide a lens through which to explore initiation of injectable therapy [53]. Realist evaluations explore how context interacts with a mechanism to produce an outcome. In this study:The context is the management of a person with T2D in primary care, where the primary care clinician should take a holistic view of the benefit-risk of any treatment option.The mechanism(s) are complex. There are evidence-based guidelines about intensification of treatment [54]; there are financial incentives to ensure that patients achieve glycaemic control [27]; and prompts that appear in the consultation [55].The outcome measure is the commencement of injectable therapy, in accordance with National Institute for Health and Care Excellence (NICE) guidance [54].

Critical realism attempts to answer the questions “What works, for whom, in what circumstances, in what respects, and why?” [56]. Our focus groups and direct observation of the clinical consultation (video of simulated surgery), and our consensus exercise will set out to explore these. This is in contrast to the traditional approach used in interventional studies (such as randomised controlled trials) which focus on whether an intervention works or not, without in-depth consideration of the context or analysis of the mechanisms [57].

### Theoretical framework – model of pathways to treatment

To help us interpret and understand the different pathways to initiating injectable therapy in people with T2D, we will use the Model of Pathways to Treatment as a theoretical framework [58]. This has previously been used to explore different care pathways in cancer research [59, 60], but has been little used in diabetes. The model pinpoints five key time points, “events”, that might occur before a health care professional starts treatment in an individual. These events include, (1) an individual identifying physical changes in the body; (2) realising that these symptoms are abnormal and should be discussed with a health care professional; (3) discussing concerns about the body changes with a health care professional for the first time; (4) the time point at which a diagnosis is made; and (5) commencement of treatment. The time periods, “intervals”, that occur between each event are factored into the model, as well as “processes”, which take place within the intervals and can trigger the successive event.

### Sample selection

Participants will be purposively sampled to ensure that a range of individual characteristics are represented within the staff (years in practice, diabetes experience) and patient (diabetes duration, ethnicity, socioeconomic status) focus groups [61]. Our sample will be restricted, for travelling reasons, to within 50 miles of our University location. Effectively, this is to London and the southeast of England. We will select practices that are broadly similar to other general practices in England in terms of size, prevalence of patients with T2D, their age, gender, ethnicity, deprivation, glycaemic control and threshold for prescribing injectable therapy. We report the sampling methods in more detail in the following sections.

### Data collection

#### Phase 1 – Focus groups and interviews

Phase 1 comprises separate focus groups, or interviews, with patients and clinicians. We will conduct separate focus groups for the different participating groups to minimise response bias: (1) patients, and (2) primary care clinicians.

Topics for the patient group will include:(i)Views on initiating injectable therapy(ii)Facilitators and barriers affecting initiation and adherence to injectable therapy(iii)Other factors that affect decision-making.

Clinician topics will be:(i)Reflection on their personal decision-making processes(ii)Insights into barriers and facilitators to initiation and adherence to injectable therapy.

Whilst interaction within focus groups may identify themes that may not emerge in individual interviews [62], we may have to offer interviews when participants find focus groups daunting, or where there are difficulties with scheduling. The focus groups will comprise six to eight participants - the recommended number for this method [63].

We plan to conduct two patient focus groups and two practitioner focus groups. Within each study practice, we will recruit patients with T2D who are naïve to injectable therapy, and others who have prior experience of GLP-1 RAs and/or of insulin. The moderator will introduce the topics under discussion, monitor group dynamics to ensure that all participants have the opportunity to share their views, are adequately represented, and all topics are covered. A second moderator will be present to take detailed notes of the discussion and help the moderator keep to times. The focus groups will last between 90 to 120 min. The focus groups and interviews will be recorded and transcribed *verbatim* [50].

Pilot focus groups will be conducted to inform the interview schedules. One pilot focus group will be conducted with clinicians, and another with T2D patients.

##### Participant inclusion criteria

The following people will be eligible for phase 1 of the study:Aged 18 years or olderA recorded and physician-confirmed diagnosis T2DEnglish speakingA registered patient with one of the participating RCGP RSC practices.

Primary care clinicians will also be eligible for inclusion if they are a GP or a practice nurse working at one of the participating practices.

#### Phase 2 – a) Video-recorded simulated surgeries

We will conduct video-recorded simulated surgeries with GPs and follow-up focus groups. These will capture the context within which escalation to injectable therapy occurs. It will also provide direct observation of the components of the clinical consultation that are not routinely recorded in CMRs, such as clinicians’ approach towards care (shared or non-shared decision-making with patients). We hope to reproduce the prompts and access to guidelines that GPs generally see.

Six GPs and three actors will participate in a diabetes clinic run at their practices. Actors will be accessed through the RCGP Clinical Skills Assessment (CSA), as they have experience in simulated surgeries within a primary care environment, and through our contacts with patients with T2D. Concepts communicated by participants in Phase 1 will be used to inform scenarios involving initiation of injectable therapy (insulin and GLP-1 RAs), which will then be given to the actors.

The scenarios will include: (1) a simulated patient where injectable therapy is probably not needed (Additional file 1); (2) a simulated patient who should be initiated on insulin (Additional file 2); and (3) a simulated patient who should be initiated on a GLP-1 RA (Additional file 3).

The actors will present their scenario to each of the clinicians in rotation, which will be video-recorded using the Activity Log File Aggregation (ALFA) toolkit [64]. The booked duration of each consultation will be 20 min; they will be stopped at 22 min. Most general practice diabetes clinics allow 20 min for consultations, though some follow-up is done in 10 min.

The ALFA toolkit is a multi-channel video method to capture the precise observation of the clinical consultation such as verbal and non-verbal cues, and the impact of the computer, through capturing different streams of data [64, 65]. The ALFA toolkit records four streams of data; (1) clinician’s upper body, (2) patient’s upper body, (3) wider angle capturing both patient and clinician, and (4) the clinician’s computer screen. The videos will be stored on encrypted and password protected hard drives.

#### b) Follow-up focus groups – including assessing consensus statements

The GPs that take part in the simulated surgeries will be asked to participate in a follow-up focus group to discuss the scenarios that were presented to them. In addition, we will present the GPs with consensus statements to explore where there is a consensus or disagreement about the facilitators and barriers to intensification of treatment to injectable therapy [66]. These statements will be generated using the findings of the focus groups in phase 1. Such a process often assists to produce recommendations or issue statements that can be used for understanding the current state of care and assist in related policy development or process improvement [67–70]. The consensus statements will be subjected to an expert panel review (the GPs in this instance) during which they will indicate the appropriateness of each statement using a Likert scale similar to that used in Delphi studies [71]. The feedback will be used to revise the consensus statements and sent for a further round of consensus to the same expert panel.

##### Participant inclusion criteria

Up to six GPs working at one of the participating practices will participate in phase 2, and also three actors accessed via the RCGP CSA and through contact with patients with T2D.

#### Phase 3 – Quantitative surveys /consensus exercise

We will use the findings from phases 1 and 2 (Round 1) to develop an online survey for clinicians, to capture the degree of consensus with our phase 1 and 2 findings (Round 2) (Fig. 2). The surveys will include statements for respondents to agree or disagree with. There will also be an opportunity for the respondents to explain why they agree or disagree with a statement.Generating consensus statements: This will be a selective round where the information captured in the research so far will be converted into a set of consensus statements (Round 2). The information captured from patients will be used to formulate a set of consensus statements for representing patient views, whilst information captured from the clinicians will be used to formulate a similar set of statements representing the views of clinicians. These consensus statements will be presented to the GPs during the follow-up focus groups in Phase 2. The clinicians will be expected to indicate the appropriateness of each of the statements using a 7 point Likert scale (Round 2).Looking for agreement, equivocation or disagreement with the consensus statements: During this final round the statements generated will be analysed and results will be presented to the clinicians as an online report (and survey to collect opinions about the results) (Round 3). This will be carried out in parallel to phase 3. For each of the statements, we will indicate if the panel of clinicians in round 1 were in agreement, disagreement or equivocal. During the presentations, the clinicians will be invited to express their opinion about the various levels of agreement assigned to the statements. In cases, where the majority of statements are not acceptable to the panel, we will consider conducting an additional round of consensus after revising the statements.This report will be shared with clinicians during the final round of the consensus process whereby the clinicians will be invited to suggest possible reasons for the any disagreements expressed during the evolution of the consensus document (Round 3).

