##### Participant inclusion criteria

Experts that have a substantial amount of experience caring for people with T2D in the primary care setting (Round 2). We will also involve clinicians in the wider RCGP RSC network to explore whether the consensus feedback is relatable to their primary care setting (Round 3).

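### The only round expressly given to wider-network clinicians shows them the panel's verdict before asking their view, so its answers cannot be reported as independent network agreement

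*Protocol article*

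**What the plan says.** Study design and setting describes a quantitative component in which themes from the earlier work are compared "with other practices in the network via a survey to explore consensus".

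The section on the Phase 3 surveys and consensus exercise then describes two things. The first is an online survey of clinicians, labelled Round 2, with statements to accept or reject and room to explain why. No panel result is mentioned there. The second is Round 3, where "results will be presented to the clinicians as an online report (and survey to collect opinions about the results) (Round 3". For that round the article says: "For each of the statements, we will indicate if the panel of clinicians in round 1 were in agreement, disagreement or equivocal". The task set is that "the clinicians will be invited to express their opinion about the various levels of agreement assigned to the statements", and clinicians may also suggest reasons for disagreement. This is said to run alongside phase 3.

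The Phase 3 inclusion criteria allocate people to rounds. Round 2 is for "Experts that have a substantial amount of experience caring for people with T2D in the primary care setting (Round 2". For Round 3 the investigators will "involve clinicians in the wider RCGP RSC network to explore whether the consensus feedback is relatable to their primary care setting (Round 3".

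The GP panel that rates statements in Phase 2 is small: "Up to six GPs working at one of the participating practices will participate in phase 2".

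**The concern.** Feeding group results back is sound when the recipients have already rated. The Phase 2 follow-up does this: the GPs rate the statements, the statements are revised, and they return to the same GPs. Wider-network clinicians are in a different position. No passage clearly records a rating from them before they see the panel's label, and the question put to them concerns the label rather than the statement.

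A displayed verdict can draw answers towards it. If Round 3 answers were used for the comparison in Study design and setting, agreement between network and panel could partly reflect what the respondents had just been shown. An uninfluenced view that was never collected cannot be recovered at analysis. The stake is real because the panel is at most six GPs, recruitment is restricted for travel to within 50 miles of the university, and describing consensus and discrepancy among clinicians and patients is a primary objective. The network survey is meant to take the question to other practices.

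**Working it through.** The document gives no sample size, threshold or effect for Phase 3, so no arithmetic applies. The check is to set the sections side by side and ask whether any of them secures a network rating made before the panel result is seen.

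1. **Purpose of the network survey.** Study design and setting: compare earlier themes with other practices and explore consensus. This requires the other practices' own opinion of each statement.

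2. **Who is in which round.** Phase 3 inclusion criteria: experienced experts in Round 2; wider-network clinicians in Round 3. The network is not named for Round 2.

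3. **What Round 3 shows and asks.** Phase 3 section: a report with a panel label on every statement (agreement, disagreement or equivocal), then a request for opinions on the labels. The verdict comes first and is itself the subject of the question.

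4. **Whether the direct survey fills the gap.** The agree/disagree survey at the start of the Phase 3 section would give an unprompted rating if network clinicians completed it. It is addressed only to clinicians in general and carries the Round 2 label. Combining this with step 2, its respondents on the literal text are the experts. A network rating is therefore possible but not secured.

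5. **Whether the round labels can settle it.** They cannot. The 7-point rating by the GPs is labelled Round 2, while the sentence on feedback refers to the panel's position in Round 1, a label the same section gives to the findings of phases 1 and 2. Round 3 is described as running in parallel to phase 3 although it is set out under the Phase 3 heading.

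6. **What the analysis would do with the answers.** Data analysis, Phase 3: each statement is summarised as agreement, disagreement or equivocation from the spread of Likert responses. If Round 3 answers fed this summary, a shift towards the displayed label would pass straight into the reported category.

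Result: step 1 needs an uninfluenced network rating, step 3 does not provide one, and steps 4 and 5 leave it uncertain whether anything else does.

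**The case against.** The strongest reply is that Round 3 is being judged against an aim it was not given. The inclusion criteria state its purpose as finding out whether the consensus feedback is relatable to respondents' own settings, and the Phase 3 section adds asking for reasons behind disagreements. Neither can be done without showing the results. This stands: disclosure is proper for that aim, and the article never calls Round 3 an independent check.

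A second reply is that the comparison in Study design and setting may belong to the direct agree/disagree survey, so the network may well rate unprompted. This also stands as a possibility. A reader might infer that network clinicians certainly see the verdict before any rating, or that Round 3 is the only contact with them. The document supports neither. It also leaves open whether earlier raters are among the Round 3 clinicians, since it refers to statements not being acceptable to the panel. Fig. 2, which sets out the consensus pathway, is not reproduced in the text reviewed and may show the order.

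A third reply is that anchoring is only a risk. That is right. A reader might go further and conclude that network agreement will be inflated, but nothing in the document fixes the size of any shift, and a label of disagreement or equivocal would pull in a different direction from a label of agreement.

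What survives is narrower. The written text gives the network survey a comparison role, expressly places network clinicians only in the round that discloses the verdict, and does not secure their own rating beforehand. This is not merely detail left to a fuller protocol, because the article itself states the Round 3 content and task and allocates respondents to rounds.

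**Conclusion.** The point holds in a limited form. Round 3 answers, as described, are open to anchoring and cannot be reported as independent agreement by the network. The size and direction of any effect are unknown, and no figure is offered because any figure would rest on invented inputs. Phase 3 is analysed descriptively, so no test or error rate is affected; what is at risk is the interpretation of the agreement categories.

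The conclusion assumes that the inclusion criteria mean what they say, with experts in Round 2 and the wider network in Round 3. If network clinicians in fact complete the direct survey before receiving the report, the design already holds the rating it needs and the fault is confined to inconsistent labelling. The change is worth making in either case because it is cheap while the survey is still to be developed.

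**What to change.** In the network survey, present each statement first without any panel label and collect the respondent's own rating on the 7-point scale already planned for the GPs. Then show the panel result and ask about relatability and reasons for disagreement, without allowing a return to the first rating. Use the unlabelled rating for the comparison promised in Study design and setting, and report comments on the labels separately as relatability.

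If network clinicians already complete the direct survey before the report, keep that arrangement and align the round labels in the Phase 3 section and its inclusion criteria so that this is explicit. Correct the reference to the panel's position in Round 1 at the same time. If no prior rating is to be collected, limit Round 3 conclusions to relatability and make no claim of network agreement from them.

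The cost is about one extra response per statement and a change of page order in an online form. The feedback step is kept in full.
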